## Abstract

**Background:**

Prevention and early detection of colorectal cancer (CRC) is a global priority, with many countries conducting population-based CRC screening programs. Although colonoscopy is the most accurate diagnostic method for early CRC detection, adherence remains low because of its invasiveness and the need for extensive bowel preparation. Non-invasive fecal occult blood tests or fecal immunochemical tests are available; however, their sensitivity is relatively low. Syndecan-2 (*SDC2*) is a stool-based DNA methylation marker used for early detection of CRC. Using the EarlyTect™-Colon Cancer test, the sensitivity and specificity of *SDC2* methylation in stool DNA for detecting CRC were previously demonstrated to be greater than 90%. Therefore, a larger trial to validate its use for CRC screening in asymptomatic populations is now required.

**Methods:**

All participants will collect their stool (at least 20 g) before undergoing screening colonoscopy. The samples will be sent to a central laboratory for analysis. Stool DNA will be isolated using a GT Stool DNA Extraction kit, according to the manufacturer’s protocol. Before performing the methylation test, stool DNA (2 µg per reaction) will be treated with bisulfite, according to manufacturer’s instructions. *SDC2* and *COL2A1* control reactions will be performed in a single tube. The *SDC2* methylation test will be performed using an AB 7500 Fast Real-time PCR system. C_T_ values will be calculated using the 7500 software accompanying the instrument. Results from the EarlyTect™-Colon Cancer test will be compared against those obtained from colonoscopy and any corresponding diagnostic histopathology from clinically significant biopsied or subsequently excised lesions. Based on these results, participants will be divided into three groups: CRC, polyp, and negative. The following clinical data will be recorded for the participants: sex, age, colonoscopy results, and clinical stage (for CRC cases).

**Discussion:**

This trial investigates the clinical performance of a device that allows quantitative detection of a single DNA marker, *SDC2* methylation, in human stool DNA in asymptomatic populations. The results of this trial are expected to be beneficial for CRC screening and may help make colonoscopy a selective procedure used only in populations with a high risk of CRC.

*Trial registration*: This trial (NCT04304131) was registered at ClinicalTrials.gov on March 11, 2020 and is available at https://clinicaltrials.gov/ct2/show/NCT04304131?cond=NCT04304131&draw=2&rank=1.

## Background

Colorectal cancer (CRC) is the second leading cause of cancer-related death worldwide [1]. Studies estimate that more than 250,000 new cases of CRC and approximately 9000 CRC-related deaths will occur in 2020 in South Korea [2]. The mean 5-year survival rate for early-stage CRC can be as high as 90% but can be less than 10% if metastasis occurs [3]. Therefore, prevention and early detection of CRC has emerged as a significant global initiative, and many countries conduct population-based CRC screening programs [4]. Although colonoscopy is the most accurate diagnostic method for early CRC detection, adherence remains very low due to the invasiveness of the procedure and the need for extensive bowel preparation [5, 6]. Sigmoidoscopy without bowel preparation can be used instead of colonoscopy, but it fails to detect abnormalities between the cecum and sigmoid colon. Digital rectal examination is the easiest diagnostic method, but it is only useful for detecting rectal cancer. Although computed tomography (CT) colonography is a non-invasive method that can visualize the proximal colon above the obstructing lesion in extraluminal views, it is not as accurate as colonoscopy [7]. Noninvasive fecal occult blood tests and fecal immunochemical tests (FITs) are also available; however, their sensitivity is relatively low [8]. As an alternative to overcome these limitations, noninvasive, simple, and accurate molecular diagnostic tests using bodily fluids or feces have been gaining attention. These tests may be used for screening in patients reluctant to undergo screening colonoscopies, thereby allowing colonoscopy to be selectively performed in specific cases to detect early-stage CRC.

CRC arises from an accumulation of genetic and epigenetic abnormalities in the genome [9], including DNA methylation, in which methyl (CH_3_) groups are added to the 5′ position of cytosine (C) in the CpG island of a DNA molecule. Aberrant DNA methylation is associated with tumorigenesis of all types of cancer and has been established as one of the most common molecular alterations in CRC [10–12]. Therefore, specific DNA sites that are aberrantly methylated in colorectal neoplasms are well recognized as potential non-invasive molecular biomarkers for early CRC detection.

Regulatory regions in most genes consist of a sequence dense with CpG islands. If methylation occurs at the gene regulatory region, structural changes in chromatin, including in the CpG island, are induced, resulting in gene silencing [13]. Aberrant DNA methylation often occurs prior to genetic alterations. Thus, abnormal DNA methylation of certain genes may occur in progressive cancer, as well as in precancerous lesions (e.g., adenomatous polyps). Therefore, the presence of methylation of specific genes could be used as a biomarker for the diagnosis of early-stage cancer [14]. Targeting cancer-specific methylated DNA for early cancer detection has many advantages, when compared with other known biomarkers [15].

In cancer tissues, abnormally methylated DNA sites are often shed into the blood and circulate in the form of cell-free DNA. In addition, exfoliated cells from the colonic mucosa are frequently present in feces. Because stool specimens from CRC patients usually contain exfoliated tumor cells, stool-derived DNA testing has emerged as a new strategy for the non-invasive detection of CRC and its precursor lesions [16]. We previously identified syndecan-2 (*SDC2*) as a potential stool-based DNA methylation marker for early CRC detection [17, 18]. Moreover, we reported that detecting *SDC2* methylation has greater than 90% sensitivity and specificity, suggesting that this strategy would be an excellent non-invasive screening test for early diagnosis of CRC [19]. Here, we report the protocol of a larger trial to validate the use of *SDC2* methylation detection in stool DNA as a screening method for CRC in asymptomatic populations.

## Methods/design

### Study design

This study is a prospective, multicenter trial to evaluate the clinical performance of a device (EarlyTect™-Colon Cancer, Genomictree, Daejeon, Korea) that allows for the quantitative detection of a single DNA marker, *SDC2* methylation, in human stool DNA from asymptomatic individuals.

Before the study is initiated, the staff will be trained in all aspects of the study, including the assay procedure and instrument use. All eligible participants scheduled for colonoscopy for any reason will be enrolled in this trial. Before initiating bowel preparation for colonoscopy, all participants will collect at least 20 g of their stool using a plastic collection tube (50 mL) that is included in the kit. The following samples will be considered inappropriate for analysis and excluded: diarrhea or loose stool, quantities less than 20 g, samples collected during bowel preparation, and samples submitted over 2 weeks after collection. Samples collected by the participant for the EarlyTect™-Colon Cancer test will be sent to a central laboratory.

Stool DNA will be isolated using a GT Stool DNA Extraction kit (Genomictree, Inc, Daejeon, Korea) according to the following instructions:All stool samples will be weighed and thoroughly homogenized in the preservative buffer using a multiple vortexer (Thermo Fisher Scientific, Waltham, MA, USA). After homogenization, 2–4 g equivalent of each stool sample will be collected and centrifuged at 2,000 rpm for 2 min (HA-1000-3; Hanil Science Medical, Daejeon, Korea).The supernatants will be discarded, and the pellet will be resuspended in 5.0 mL lysis buffer 1 (Genomictree, Inc, Daejeon, Korea) before incubating for 4 min at room temperature.The samples will be centrifuged at 2000 rpm for 2 min, and the supernatant will be discarded before adding 2.0 mL lysis buffer 2 (Genomictree, Inc, Daejeon, Korea) and 30 μL proteinase K (0.4 mg/mL, Sigma-Aldrich, St. Louis, MO, USA). The samples will then be incubated at 70 °C for 10 min.The samples will be centrifuged at 3000 rpm for 5 min, and 0.75 mL supernatant will be added to the MaXtract High-Density tube (Qiagen, Hilden, Germany). Tris-saturated phenol–chloroform-isoamylalcohol (25:24:1 [v/v]; Sigma-Aldrich, St. Louis, MO, USA) will then be added to the samples.The samples will be thoroughly mixed for 1 min and then centrifuged in a microcentrifuge at maximum speed for 10 min. The supernatant (0.5 mL) will be transferred to a new tube, and 1/10 volume of 3 mol/L sodium acetate (pH 5.2; Welgene, Gyeongsan, Korea) and an equal volume of isopropanol (Merck, Darmstadt, Germany) will be added to the sample.Total nucleic acid will then be precipitated by centrifugation at maximum speed for 10 min. The DNA pellet will be washed with 1.0 mL 70% ethanol and dried. DNA concentration will be measured using the Qubit dsDNA BR Assay Kit (Thermo Fisher Scientific, Waltham, MA, USA). A solid phase magnetic bead-based stool DNA extraction method will also be available.

All information regarding the stool sample will be anonymized at the time of examination, treated as blind (single-blind) to the operator, and randomly assigned a unique number. The sample will then be sent to a central laboratory to test for *SDC2* methylation. After study enrollment is complete, the methylation analysis results will be disclosed. The results and case report form (CRF) will be compared and analyzed to evaluate the sensitivity and specificity of the EarlyTect™-Colon Cancer test. Residual stool samples may be archived for further research. Clinical data and samples will be maintained in a manner that preserves the anonymity of all subjects. Specimens will be stored for 5 years in the on-site biorepository of the central laboratory for potential use in future research. A schematic diagram of the trial workflow is depicted in Fig. 1.

**Fig. 1 Fig1:**
[figure not shown]
Schematic diagram of the workflow of the trial

The *SDC2* methylation test will be performed according to the GT-CRC-UM-701 protocol (provided by the Sponsor) using the AB 7500 Fast Real-time PCR System (Thermo Fisher Scientific, Waltham, MA, USA). Briefly, 2 µg stool-derived genomic DNA will be chemically modified with sodium bisulfite using the EZ DNA Methylation-Gold kit (ZYMO Research, USA), according to the manufacturer’s instructions. For PCR analysis, *SDC2* and *COL2A1* control reactions will be performed twice in a single tube, as previously described [18, 19]. C_T_ values will be calculated using the software accompanying the AB 7500 Fast Real-Time PCR System. *SDC2* methylation will be considered detected if C_T_ is less than 40 cycles and not detected if C_T_ is not measurable [17]. To maximize clinical sensitivity, *SDC2* methylation will be considered positive if at least one of two PCR reactions has detectable methylated *SDC2*. Thus, samples will be categorized as positive if at least one of two reactions (1/2 algorithm) has detectable *SDC2* and considered negative if *SDC2* methylation is not measurable in both reactions. Our previous clinical study showed that the 95% limit of detection of the EarlyTect™-Colon Cancer assay was 34.5 pg, corresponding to approximately 20 diploid genome copies [19]. Reproducibility and repeatability of the assay were acceptable, within a coefficient of variation of 5%. A total of 23 potential interfering substances, selected because of their clinical and dietary uses in South Korea, were confirmed to have no effect on the test performance of EarlyTect™-Colon Cancer assay. The assay also exhibited no cross-reactivity, even when excess amounts (10^5^–10^6^ genome copies) of bacterial and viral DNA were tested.

Results from the EarlyTect™-Colon Cancer test will be compared against those obtained by colonoscopy and any corresponding diagnostic histopathology from clinically significant biopsied or subsequently excised lesions. Based on these results, participants will be divided into three groups: CRC (group 1), polyp (group 2), and negative (control). The following clinical data will be recorded for the participants: sex, age, colonoscopy results, and clinical stage (in the CRC case group).

Participant selection criteria are as follows:

*Inclusion Criteria*No symptoms suggestive of CRC.The individual provides written informed consent.The individual is at least 60 years old when they receive a colonoscopy.Criteria for high-risk CRC patients younger than 60 years old who will participate in the trial are as follows:At least one parent and/or sibling was diagnosed with colorectal cancer before age 55 years.One of his/her parents, brothers, and sisters was diagnosed with colorectal cancer after age 55 years.More than two of his/her parents, brothers, and sisters were diagnosed with colorectal cancer.Previous polypectomy for pathologically confirmed adenoma (at least 1 year ago).Occurrence of inflammatory bowel disease (diagnosed at least 15 years ago).5.The individual provides more than 20 g of his/her stool for analysis.

*Exclusion Criteria*Younger than 60 years and does not meet the aforementioned high-risk criteria.Receiving or has received any type of therapy for CRC.Less than 20 g of stool is provided for analysis.Stool is considered inadequate for analysis (e.g., diarrhea or loose stool).

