### Objective

This trial aims to validate the use of *SDC2* methylation in stool DNA for early detection of CRC in asymptomatic populations. The primary endpoint of this study is to evaluate the sensitivity and specificity of the EarlyTect™-Colon Cancer for detecting CRC.

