### Sample size calculation

Because this is not a randomized controlled trial, a statistical calculation for comparative analysis was not considered. Instead, we have assumed that the prevalence of colon polyps in Korea is 25% based on our previous pilot study, in which we found an 80% sensitivity of EarlyTect™-Colon Cancer for detecting CRC and polyps in 585 patients [19]. Therefore, at least 476 participants are needed to identify polyps or cancers. In our previous study, we intentionally controlled the types of cases (i.e., 245 CRC, 44 adenomatous polyps, and 245 negative colonoscopy results). However, we will enroll more than two times the number of cases (n = 1000) in this trial and specifically include asymptomatic participants who will undergo colonoscopy. Assuming a drop-out rate of 10%, 1112 participants will be enrolled in this trial.

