### Statistical analysis

To calculate sensitivity and specificity, the test results will be denoted with dichotomous variables, namely “1” for methylation-positive individuals and “0” for methylation-negative individuals. Sensitivity and specificity for CRC detection, area under the curve (AUC) value, and 95% confidence interval (CI) will be calculated using receiver operating characteristics (ROC) analysis (SAS v.9.4). The cut-off value for C_T_ will be less than 40, and the following endpoints will be assessed:True positive (TP): *SDC2* methylation-positive in CRC patientsTrue negative (TN): *SDC2* methylation-negative in the control (negative) subjectsFalse-positive (FP): *SDC2* methylation-positive in the control subjectsFalse-negative (FN): *SDC2* methylation-negative in CRC patientsSensitivity = 100 × TP/(TP + FN)Specificity = 100 × TN/(TN + FP)Negative predictive value (NPV) = TN/(TN + FN)Positive predictive value (PPV) = TP/(TP + FP)

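### Participants in the undefined polyp group count in neither specificity nor PPV, although both measures are for colorectal cancer and a positive test in any of them is a false positive for that target

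*Protocol article*

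**What the plan says.** Under Study design, test results are compared with colonoscopy and "any corresponding diagnostic histopathology from clinically significant biopsied or subsequently excised lesions". On that basis "participants will be divided into three groups: CRC (group 1), polyp (group 2), and negative (control"). No histological type, grade or size is given for group 2. The clinical data listed for recording are "sex, age, colonoscopy results, and clinical stage (in the CRC case group"); polyp histology is not named.

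The Objective section sets the primary endpoint: to "evaluate the sensitivity and specificity of the EarlyTect™-Colon Cancer for detecting CRC". The Statistical analysis section defines true positives and false negatives in CRC patients, and true negatives and false positives in control (negative) subjects. It then gives "Specificity = 100 × TN/(TN + FP") and builds PPV and NPV from the same four counts. Group 2 appears in none of them.

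The Sample size calculation says "we have assumed that the prevalence of colon polyps in Korea is 25% based on our previous pilot study", without limiting the polyps by type. The pilot is described there as "245 CRC, 44 adenomatous polyps, and 245 negative colonoscopy results". The Background names adenomatous polyps when it explains why methylation may appear before cancer: abnormal methylation may occur in cancer "as well as in precancerous lesions (e.g., adenomatous polyps").

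**The concern.** If the target is CRC, everyone without CRC is target-negative, and a positive test in any of them is a false positive. The stated definitions instead compare the two ends of the spectrum, cancers against clean colonoscopies, and leave out the people in between. Many of those in between have lesions in which, by the article's own rationale, the marker may be positive. A specificity from clean colonoscopies alone may therefore be higher than the test would show in the people it is meant to screen. PPV is affected more directly, because every positive in group 2 is missing from its denominator.

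The missing definition adds a second problem. A participant with only a non-neoplastic polyp does not have a negative colonoscopy in the ordinary sense and so falls into group 2. Any positivity rate reported for that group would then mix adenomas with lesions that are not precursors. It would not be directly comparable with the adenomatous polyps listed for the pilot unless adenomas were separated.

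**Working it through.** **The plan's own figures.** 1000/(1 − 0.10) = 1111.1, rounded up to 1112, which matches the stated enrolment. At 25% prevalence, group 2 holds 0.25 × 1000 = 250 people. The point changes denominators, not the sample size.

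**Assumptions (not in the article).** 5 CRCs among 1000 evaluable participants; 90% sensitivity; 90% specificity in controls. Controls = 1000 − 250 − 5 = 745.

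**As the article defines the measures.** TP = 0.9 × 5 = 4.5. FP = 0.1 × 745 = 74.5. TN = 670.5.
- Specificity = 670.5/745 = 90.0%.
- PPV = 4.5/(4.5 + 74.5) = 4.5/79 = 5.7%.

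**Group-2 positivity.** The article gives no rate. With assumed positivity of 40% (advanced adenoma), 20% (other adenoma) and 8% (non-neoplastic):
- shares 0.1/0.5/0.4: 0.040 + 0.100 + 0.032 = 0.172
- shares 0.3/0.5/0.2: 0.120 + 0.100 + 0.016 = 0.236

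**All 995 non-CRC participants.** With positivity q in group 2, specificity = [670.5 + 250(1 − q)]/995 and PPV = 4.5/(79 + 250q).

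| q | Group-2 positives | Specificity | PPV |
|---|---|---|---|
| 8% | 20 | 900.5/995 = 90.5% | 4.5/99 = 4.5% |
| 10% | 25 | 895.5/995 = 90.0% | 4.5/104 = 4.3% |
| 17.2% | 43 | 877.5/995 = 88.2% | 4.5/122 = 3.7% |
| 23.6% | 59 | 861.5/995 = 86.6% | 4.5/138 = 3.3% |

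The change in specificity is (250/995) × (0.10 − q). It is a fall only if group 2 is positive more often than controls. PPV falls for any q above zero. For scale, the 95% half-width at 90% specificity in 745 controls is 1.96 × √(0.9 × 0.1/745) = 2.2 percentage points. The falls of 1.8 and 3.4 points are of that order.

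**Returning only non-neoplastic polyps.** If 20–40% of group 2 is non-neoplastic only, 50–100 people move. At 8% positivity they add 4–8 false positives:
- Specificity = 1 − 78.5/795 = 90.1% to 1 − 82.5/845 = 90.2%.
- PPV = 4.5/83 = 5.4% to 4.5/87 = 5.2%.

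Over a wider grid (10–50% non-neoplastic, 10–30% positivity) specificity runs from 90.0% down to 87.1%. The low end needs 125 people at 30% positivity: (670.5 + 87.5)/870.

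**Pilot figures.** The listed groups sum to 245 + 44 + 245 = 534, which is 51 short of the 585 cited. Of the 289 listed lesions, 245 (85%) are CRC.

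**The case against.** The best reply is that this is an undefined label in a condensed article. Lesion categories are usually spelt out in the full protocol or the case report form, and comparing CRC with clean colonoscopies is a legitimate specificity. The first part stands as far as it goes: a full protocol may define polyps more closely. It does not answer the main point, because the article does state who counts as a true negative and a false positive, and those definitions exclude group 2 however it is defined. As for the second part, negative-colonoscopy specificity is worth reporting, but it should not be the only specificity when the endpoint is detection of CRC.

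The objection also rightly limits the point in these respects:

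- A reader might infer that histology is obtained but ignored in the grouping. The text says otherwise: histopathology of clinically significant lesions is among the results on which the grouping rests.
- A reader might take it as stated that non-neoplastic polyps are pooled with adenomas. It is not stated. It follows from the plain reading, and a participant with only a hyperplastic polyp could still be classed as negative.
- A reader might conclude that planning relied on adenoma-only data. The 80% sensitivity is for CRC and polyps together, most of the listed lesions are CRC, and the 51 unlisted patients are of unknown type.
- The article plans no accuracy measure for group 2, so it cannot be faulted for misreporting one.
- Moving only the non-neoplastic polyps may change specificity by a few tenths of a point, possibly upwards, which is well inside sampling error.

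**Conclusion.** The point holds and should be acted on. By the stated definitions about a quarter of evaluable participants, adenomas included, count in neither specificity nor PPV for CRC, and the article does not say where non-neoplastic polyps go. Under the assumptions shown, specificity in all non-CRC participants would be about 87–88% instead of 90%, and PPV about 3–4% instead of 5.7%. The direction for PPV is certain if anyone in group 2 tests positive. The direction for specificity depends on whether group 2 is positive more often than controls, which the article's rationale suggests but does not quantify. The CRC count, lesion mix, positivity rates and baseline accuracy are all assumed. Sensitivity is unaffected.

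The stronger conclusion that group 2 can never be compared with the pilot is not supported: an adenoma subgroup could be compared if histology is kept.

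**What to change.** Before methylation results are disclosed:

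1. Add polyp histology to the case report form.
2. Define group 2 by most advanced lesion: advanced adenoma (with its definition written out, since the article does not use the term), other adenoma or neoplastic polyp, and non-neoplastic only. State a default category for polyps without histology.
3. Count participants with only non-neoplastic polyps as true negatives or false positives.
4. Report specificity and PPV in all non-CRC participants, alongside specificity in negative-colonoscopy participants.
5. Report test positivity with an exact 95% confidence interval for each lesion category, so that adenoma positivity can be separated from any-polyp positivity.

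The cost is wording and one case report form field, with no new procedure. Study design says that methylation results are disclosed only after enrolment is complete, and Study status gives 231 enrolled at submission against 1112 planned, so as of that date the rule could still be set blind. For those already enrolled, histology would have to be taken from existing reports. The drawbacks are that specificity may look less favourable, PPV will be lower, the advanced-adenoma category will be small with a wide interval, and polyps that were not biopsied depend on the default category.
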